#### Measures

All outcome parameters are assessed via the dedicated smartphone application ‘moma app’, which is filled in by the parents over the 9 months study duration (Fig. 2).

The app contains the following features:
Headache diary (based on established diaries [16, 17]) including a daily reminder function (missed entries days can be catched up within 2 weeks), with daily assessment of the following itemsPresence of headache (yes/no)Headache intensity (numeric rating scale 0–10 presented as a slider)Headache duration (slider from 0 to 24 h)Missed school (yes/no)Inabilty to perform leisure activities (yes/no)Use of headache medication (yes/no, tool for recording medication and dose)2.Questionnaires are presented within the app at the start and end of the baseline (weeks − 12 and 0), at the end of the intervention (week 12) and at the end of the follow-up (week 24). The following questionnaires are used:PedMIDAS (Pediatric Migraine Disability assessment score) [18]KINDL [19] (German tool for assessing pediatric quality of life).3.At the time points used for the questionnaires, the smartphone app also asks fortypical triggers of headache in the last 3 months (within the categories: school stress, family problems, conflicts with friends, noise, sport, inactivity, weather, lack of sleep, drinks containing caffeine, reduced fluid intake, high use of electronic media, infection, others)headache prophylactic measures taken in the last 3 months (within the categories: physiotherapy, trigger point therapy, osteopathy, acupuncture, homeopathy, alternative practitioner, naturopathy, peppermint oil, magnesium, vitamin D, medication, others)

Additionally to the ‘moma App’, pediatricians in practice and social pediatric centers use the ‘moma website’ (www.moma-migraine.de) [1] to document the individual clinical presentation and characteristics of the child, for example individual migraine symptoms, important aspects of the medical history, results of the neurological examination, psychosocial factors and the therapeutic recommendations given to the family. Furthermore, they estimate the complexity of the disease for each child using the ‘moma complexity signature’, which has been developed by our group specifically for this study based on the bio-psycho-social model (see Fig. 3 for time points of data acquisition).

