### Outcome parameters

All outcome parameters are assessed via the parents’ entries in the ‘moma App’. For all outcome parameters, the difference from baseline to follow-up is measured and compared between the two groups.

The primary outcome parameter is the number of headache days per 12 weeks (84 days). Our hypothesis is that the reduction of headache days from baseline to follow-up will be at least 2 days larger for the group with interdisciplinary multimodal intervention in social pediatric centers (intervention group B) compared to the group with basic treatment in pediatric practices (intervention group A).

Secondary outcomes are:
Number of responders, defined as patients with a reduction of more than 50% of headache days per 12 weeks from baseline to follow-up;Headache intensity (averaged over headache days per 12 weeks);Number of days missed at school due to headache per 12 weeks;Number of days with cancelling of leisure activities due to headache per 12 weeks;Headache-related disability (PedMIDAS questionnaire) [18],assessed every 3 months;Quality of life (KINDL questionnaire, every 3 months) [19, 20];Number of days with intake of acute medication because of headache per 12 weeks.

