### Data analysis plan

The statistical analysis is performed according to the CONSORT Statement recommendations for cluster-randomized trials [20]. In the intention-to-treat analysis all patients having started to use the ‘moma App’ are included. Primary endpoint is the number of headache days per 12 weeks (84 days).

Two forms of analysis are performed:
Intention-to-treat analysis (“Full Analysis Set”)

All patients who started to use the electronic headache diary (moma app) and fulfill the baseline criteria (see below) are included in the intention-to-treat analysis. Patients who have less than three headache days during the 12 weeks of baseline or from whom less than 33% of the days of the headache diary are filled in during baseline are excluded and are not part of the intention-to-treat analysis.
2.On-treatment analysis (“per protocol set“)

Patients who additionally completed all 4 study visits at the pediatric practices and (only in the intervention group) the three visits at the social pediatric centers and provided electronic headache diary data with less than 33% of the days missing during the intervention and follow-up phase are included in the per protocol analysis.

For headache diary data, missing data are treated as follows. If less than 33% of the days are missing, the missing data is replaced by the mean values of the existing data. If 33 to 66% of the headache diary data is missing, a modified last observation carried forward (LOCF) approach will be performed for the intention to treat analysis. To this end, missing days are replaced by the mean values of the the last 3-month period that has less than 33% missing data. If more than 66% of the data of the headache diary data is missing, a simple LOCF principle will be applied. For this, the data of the entire 3-month period will be replaced by the mean value of the last 3-month period with less than 33% missing data.

If one or more items of the PedMIDAS (6 items) is missing, the scale will be excluded from statistical analysis of this patient at this time point because it does not retain sufficient clinical informative value.

The KINDL questionnaire (4 subscales with 4 items each) allows one missing item per subscale which is replaced by the mean value of the other items of the subscale [19, 20].

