For the primary end point (number of headache days per 12 weeks) a mixed linear regression model is performed with the difference of headache days per 12 weeks from baseline to follow-up as dependent variable, the intervention in a social pediatric center (yes/no) as independent variable and random effects for the different social pediatric centers. Age, sex and headache frequency per 12 weeks at baseline are included as possible confounders. Quality of life (KINDL) and migraine related disability (PedMIDAS) at baseline are possible effect modifying elements and therefore integrated in the model as interaction effects. The significance level α is set at < 0.05. The same model is used for analysis of the secondary outcome parameters.

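### PedMIDAS and KINDL are analysed as one change per child, so a child without a usable week-24 scale is lost despite a week-12 score; this biases the result only if the loss depends on post-baseline scores

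*Protocol article*

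**What the plan says.** All references are to the protocol article.

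- **Collection (Measures).** Both questionnaires appear in the app at weeks −12 and 0, and again "at the end of the intervention (week 12) and at the end of the follow-up (week 24").
- **Comparison (Outcome parameters).** "For all outcome parameters, the difference from baseline to follow-up is measured and compared between the two groups". PedMIDAS and KINDL are listed there as secondary outcomes.
- **Model (Data analysis plan).** The primary model takes "the difference of headache days per 12 weeks from baseline to follow-up as dependent variable". On covariates: "Age, sex and headache frequency per 12 weeks at baseline are included as possible confounders". Baseline KINDL and PedMIDAS enter as interaction effects, and centres have random effects. Then: "The same model is used for analysis of the secondary outcome parameters".
- **Missing data (Data analysis plan).** Mean replacement and carrying forward are introduced with "For headache diary data, missing data are treated as follows". If any of the six PedMIDAS items is missing, "the scale will be excluded from statistical analysis of this patient at this time point". KINDL "allows one missing item per subscale which is replaced by the mean value of the other items of the subscale".

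**The concern.** The model has one outcome value per child and no visit term. The week-12 score is neither an outcome nor a covariate. The diary replacement rules do not reach the questionnaires. A child whose week-24 scale is incomplete or absent therefore has no dependent variable and leaves the analysis, even with a full score from 12 weeks earlier.

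Quality of life stands beside headache days in the trial's stated aim. Parents do the rating and can see which treatment the child receives, and group B has three extra visits. Whether a family still answers at week 24 could therefore depend on how the child was doing at week 12, and differently in the two arms. A complete-case change score would then be off, while an analysis that also used week 12 could correct for it.

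**Working it through.** **1. Does the text lead to complete-case analysis?** The article states no figure to reproduce here, so this step rests on reading.
- PedMIDAS with a missing item: exclusion at that time point is stated. With week 24 excluded, the change cannot be formed.
- KINDL with more than one missing item in a subscale, or either questionnaire wholly absent: no rule is stated. The loss follows from the change-score model.
- Week 24 as the follow-up value: read from the questionnaire schedule under Measures. The outcome definition says only follow-up.

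**2. The six-item rule alone.** The share of scales lost is 1 − (1 − q)^6, where q is the item-missing rate (assumed; the article gives none). For q = 1%, 2% and 3% this is 1 − 0.99^6 = 5.9%, 1 − 0.98^6 = 11.4% and 1 − 0.97^6 = 16.7% per time point, if items are missing independently.

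**3. When does complete-case analysis bias the contrast?** This was checked by simulation with 2,000,000 children split 279:507 between A and B. All other inputs are assumptions:
- Scores are in SD units, higher is better, and the true B − A effect is 0.20 at weeks 12 and 24.
- Correlations are 0.65 (weeks 0–12), 0.75 (12–24) and 0.585 (0–24).
- Week-24 missingness is logistic in the week-12 score. The slope is the log-odds of leaving per SD worse.

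Three estimates of the week-24 effect:

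| Slope A / B | Missing A / B | Change, baseline-adjusted | Change, unadjusted | Using week 12 |
|---|---|---|---|---|
| 0 / 0 | 10% / 30% | 0.201 | 0.200 | 0.200 |
| 1 / 1 | 20% / 20% | 0.198 | 0.198 | 0.198 |
| 1 / 1 | 10% / 20% | 0.232 | 0.210 | 0.200 |
| 0.5 / 0 | 20% / 20% | 0.163 | 0.189 | 0.198 |
| 1 / 0 | 10% / 10% | 0.165 | 0.190 | 0.199 |
| 1 / 0 | 20% / 20% | 0.135 | 0.182 | 0.201 |
| −1 / 0 | 20% / 20% | 0.266 | 0.218 | 0.201 |
| 1 / 0 | 24% / 20% | 0.122 | 0.178 | 0.200 |

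The first row has very unequal loss and no bias. The sixth and seventh have equal loss and a bias of about 0.065 SD, one in each direction. The last row is the largest: 0.200 − 0.122 = 0.078 SD, or 39% of the assumed effect. The baseline-adjusted column is the natural reading of the plan, since baseline KINDL and PedMIDAS are in the model.

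**4. A second set of assumptions.** With a true effect of −0.30, baseline correlation 0.5 and week-12/week-24 correlation 0.4, 0.6 or 0.8:
- Loss of about 10% against 25%, unrelated to score or related only to the baseline score: bias about 0.00.
- Loss dependent on week 12 in B only: −0.02, −0.06, −0.09.
- Opposite dependence by arm, with loss of about 23% and 19%: −0.04, −0.11, −0.17.
- Using week 12 brought all of these to within 0.005.
- Loss dependent on the unseen week-24 score in B only: bias about −0.13. Using week 12 still left −0.12, −0.10, −0.06.

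**5. Precision when loss is random.** In 1,000 simulated trials of 279 and 507 children with about 20% missing, the standard error was 0.0654 for complete cases and 0.0636 with week 12, a gain of 1 − 0.0636/0.0654 = 2.8%.

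**The case against.** A reader might infer that these outcomes are biased whenever drop-out differs between the arms. The documents do not support that, and neither does the check: unequal rates are not sufficient (first row of the table) and not necessary (sixth and seventh rows).

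A reader might also take the sample size section's 20% as the expected week-24 loss. It is an upper figure for four causes together, and two of them are baseline exclusions: too much missing diary data, or fewer than three headache days. Those children are gone before the intervention. The week-24 questionnaire loss is not given and would be lower on the article's own figure.

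The remaining objections are fair and mostly stand:
- The stated exclusion rule covers only PedMIDAS with a missing item. For KINDL and absent questionnaires the loss is inferred, and a separate analysis plan may say more. However, the article itself fixes the single-difference model and confines replacement largely to the diary, so the point does not rest on silence alone.
- The larger biases need a marked difference between arms in how loss depends on the score. Milder patterns give about 0.03 to 0.04 SD, and equal dependence with equal loss gives none.
- A family that stops using the app before week 12 has neither score, and a longitudinal model does not recover it.
- Only secondary outcomes are affected. The primary outcome has its own missing-data rules.

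**Conclusion.** The point holds as a conditional weakness in two secondary outcomes. As written, PedMIDAS and KINDL are complete-case analyses of one change score, with the week-12 score collected but unused. Bias requires that week-24 missingness depend on post-baseline scores after adjustment, chiefly when that dependence or the loss rate differs by arm.

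Under the first set of assumptions, with 10% to 20% missing per arm, the baseline-adjusted bias is about 0 to 0.07 SD in either direction. It reaches 0.08 SD with 24% against 20% missing. For a change not adjusted for its own baseline it is about 0.02 SD or less. Opposite dependence in the two arms can give more, as the second set shows. None of the correlations, slopes or loss rates comes from the article, so these figures show a plausible range and do not predict this trial's bias. The change is worth making because it is cheap and rests on a weaker missing-data assumption.

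**What to change.** In the Data analysis plan, replace the single-change model for PedMIDAS and KINDL with a repeated-measures mixed model:
- outcomes: the week-12 and week-24 scores;
- fixed effects: treatment by visit, the scale's own baseline by visit, and the planned covariates;
- an unstructured within-child covariance, with the planned cluster random effect kept;
- reported result: the treatment contrast at week 24, named as the follow-up time point for these scales.

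Every child with at least one usable post-baseline score, and the baseline values the model needs, then contributes. Add a sensitivity analysis for missingness that depends on the unobserved week-24 score, because week 12 removes only part of that bias.

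The cost is analysis wording, since the week-12 scores are already collected. The downside is a somewhat larger model that assumes missingness depends only on observed scores.

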**Methods:**

The study is a nation-wide cluster-randomized study. Based on the postal codes the regions are randomly assigned to the two intervention-strategies. Children with migraine are recruited in the pediatric practices, as common outpatient-care in the German health-care system. Parents rate headache frequency, intensity and acute medication intake at a daily basis via a digital smartphone application specifically designed for the study. Migraine-related disability and quality of life are assessed every 3 months. Study duration is 9 months for every participant: 3 months of baseline at the pediatric practice (both groups); 3 months of intervention at the pediatric practice (intervention group A) or at the social pediatric center (intervention group B), respectively; 3 months of follow-up at the pediatric practice (both groups).

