**Fig. 2 Fig2:**
[figure not shown]
Study design, timelines and data acquisition

In both groups, children are diagnosed with migraine by their pediatrician in practice, included in the study and, if they have at least 3 days of headache in the baseline phase (week − 12 to 0), go on to the intervention phase (week 0–12). The intervention phase includes treatment at the pediatric practice for both groups, and treatment at the social pediatric center only for the interdisciplinary multimodal group (intervention group B). There, children are treated with the structured multimodal interdisciplinary intervention “moma” as described below. After the intervention the follow-up (week 12 to 24) is performed by the treating pediatrician in practice again.

Every participant has four study visits at the pediatric practice at time points − 12, 0, 12 and 24 weeks. The interdisciplinary multimodal intervention group has three additional study (intervention) visits at the social pediatric centers.

At the first visit, the moma web application generates a hashcode for pseudonymization of the patient, which is given to the parents by the pediatrician. The parents use the hashcode to log into the “moma App”, in which they document headache frequency, intensity and acute headache medication of their child on a daily basis.

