### Strengths and limitations

The first strength of the study is the possible positive impact of the results for the participating child with migraine and its family. The second strength is the randomized controlled design with planned nationwide participation of pediatricians in practice and of interdisciplinary social pediatric centers. The third strength is the clinical and political importance of the study subject: interdisciplinary intervention programs for children with migraine are mandated but efficacy studies in this age group are lacking.

A limitation pertains to health system differences between countries, reducing generalizability of study results. The realization of study might be cumbersome because of challenges for pediatric practices related to the current COVID-19 pandemic.

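### No outcome model has a calendar term although the two windows start 24 weeks apart, and school absence is counted without regard to how many school days each window contains

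*Protocol article*

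**What the plan says.** The Protocol article, under Study design (Overview), sets baseline at weeks −12 to 0 and intervention at weeks 0 to 12. Then: "After the intervention the follow-up (week 12 to 24) is performed by the treating pediatrician in practice again". Under Outcome parameters: "For all outcome parameters, the difference from baseline to follow-up is measured and compared between the two groups".

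Under Data analysis plan, the primary model is a linear mixed model with "the difference of headache days per 12 weeks from baseline to follow-up as dependent variable". It has a yes/no term for treatment in a social pediatric center, random effects for the centers, and interactions with baseline KINDL and PedMIDAS. On further covariates: "Age, sex and headache frequency per 12 weeks at baseline are included as possible confounders". The section applies this model to the secondary outcomes as well. Season, month of entry and school holidays appear nowhere in the article.

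One secondary outcome is "Number of days missed at school due to headache per 12 weeks". The diary item behind it, under Measures, is a yes/no entry for missed school. No listed item records whether the day was a school day.

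The trigger categories offered in the app include "school stress, family problems, conflicts with friends, noise, sport, inactivity, weather, lack of sleep", and infection further down the list.

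**The concern.** Window starts 24 weeks apart place each child's baseline and follow-up in nearly opposite parts of the year. That is close to the spacing at which an annual cycle has its largest effect on a change score. The participants are 6 to 11 years old, and several triggers on the trial's own list (school stress, weather, infection) could plausibly vary over the year.

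Two things are at stake. For headache days, a seasonal swing enters each child's change as unexplained variation, and it enters the between-arm contrast if the arms recruit in different months. For school absence, a child can miss school only on a school day, so a count per 84 calendar days partly measures the school calendar.

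**Working it through.** **Inputs from the Protocol article.** Lag between window starts 24 weeks; window length 12 weeks; target difference 2 headache days per 12 weeks; required sample 279 (A) and 507 (B); ICC 0.1; 77 regions randomised 2:1 to B and A; centers participating in 73% of B regions.

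**Assumptions, because the article gives no figure.** An annual sinusoid with amplitude *a* of 0.5, 1 or 2 headache days per 12 weeks; SD of change 5.6; 26 A clusters and 37 B clusters (77 regions split 26/51, and 73% of 51 ≈ 37). The SD is close to the 5.7 that 279/507 implies with these clusters, two-sided α 0.05 and power 0.90. Without clustering the implied SD is 8.3. The article states no SD, so its sample size can only be solved backwards, and nothing here depends on it.

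**1. Effect on one child's change.** The year has 365.25/7 = 52.18 weeks, so 24 weeks is 46% of a year, or 166°.
- Lag factor: 2·sin(π·24/52.18) = 1.98
- Averaging over a 12-week window: sin(π·12/52.18)/(π·12/52.18) = 0.915
- Product: 1.98 × 0.915 = 1.82

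The largest swing in one child's change is 1.82·*a*, which is 0.9, 1.8 and 3.6 days for *a* = 0.5, 1 and 2.

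This is for the raw change. The stated model also adjusts for baseline frequency. If the effective weight on baseline is ρ, the factor becomes 0.915·√(1 + ρ² − 2ρ·cos 166°): 1.82 at ρ = 1, 1.36 at ρ = 0.5 and 0.92 at ρ = 0. The figures below use 1.82 and are upper values in that respect.

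**2. Variance.** With entry spread evenly over the year, the added variance is (1.82·*a*)²/2 = 0.41, 1.65 and 6.60. Relative to 5.6² = 31.4 this is 1%, 5% and 21%, if it comes on top of that SD.

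**3. Between-arm contrast.** Simulated with no treatment effect (279 in 26 clusters against 507 in 37, ICC 0.1, 2,000 runs, raw difference in mean change; Monte Carlo error about 0.014 day):

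| Entry pattern | Bias at *a* = 1 | Bias at *a* = 2 |
|---|---|---|
| Both arms evenly over the year | 0.00 | −0.01 |
| Both arms in the same half-year | 0.00 | 0.02 |
| B enters 8 weeks later than A | 0.51 | 1.00 |

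In the second row each arm's own mean change moves by 0.6 (*a* = 1) or 1.3 days (*a* = 2), and the contrast does not move.

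The third row holds for one position of the half-year in the seasonal cycle. For other positions the bound is 2 × 1.82 × 0.639 × sin(π·8/52.18) = 1.07·*a* in either direction, where 0.639 averages over 26 weeks of entry.

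A milder scenario: the share entering in the favourable half-year differs by 10 or 20 percentage points between arms. The shift is 2 × (2/π) × 1.82·*a* × 0.10 = 0.23·*a*, or 0.46·*a* at 20 points.

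**4. School absence.** Twelve weeks hold 12 × 5 = 60 weekdays. With an assumed 6-week holiday in the window, 30 remain. At a constant probability of missing a school day because of headache, the expected count falls by 30/60, that is by half. No seasonal theory is needed. If both arms lose the same school days, this creates no difference between them, but any true effect on the count shrinks in the same proportion.

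**The case against.** The strongest reply is that the trial does not estimate change within an arm. It compares change between concurrent arms, allocated by randomising regions, on an identical schedule. Season and school calendar are then balanced in expectation and cancel, as the first two rows of the table show. This stands. A reader might infer from the 24-week spacing that the primary result will reflect month of entry. The documents do not support that: it holds for a child's own change or an arm's mean change, and bias in the contrast needs entry timing that differs by arm.

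Nothing in the article shows such a difference. Center participation in 73% of B regions says which regions contribute, not when children enter, and in both arms pediatricians in practice recruit. What remains is possibility: children are recruited in regions already allocated, and with 77 regions some chance imbalance in calendars can occur.

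It is also fair that the amplitudes and entry splits are assumptions, that an empirical SD of change would already contain seasonal variation, and that expected numbers (1,323 and 1,931) far exceed those required, so precision is not the binding constraint on the plan's own figures. The trigger list is a set of response options, not evidence of seasonality. The remark that "The realization of study might be cumbersome because of challenges for pediatric practices related to the current COVID-19 pandemic" says nothing about school closures.

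A last reply is that calendar terms belong in an analysis plan not shown. This carries less weight, because the article fixes a covariate list and extends it to every secondary outcome. The missing school-day denominator lies in the definition of the outcome itself.

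**Conclusion.** The point holds as a moderate improvement in precision and robustness. It does not make the primary comparison invalid.

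Certain from the document: the 24-week lag, a covariate list without a calendar term reused for all outcomes, and school absence as a raw count with no school-day denominator. Conditional on assumption: a variance cost of about 1% to 21% for amplitudes of 0.5 to 2 days on an SD of 5.6. For an 8-week difference in entry between arms, the simulated shift is 0.5 to 1.0 day at amplitudes of 1 to 2, and up to about 1.07 times the amplitude at the least favourable time of year. With equal entry timing the bias is about zero.

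School absence is the strongest part, because for an individual child the distortion is plain arithmetic. It concerns one of seven secondary outcomes, and it too is balanced between arms in expectation. The responder outcome deserves a brief mention, since it classifies each child by that child's own change.

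**What to change.** 1. Define school absence in each window as missed days divided by available school days, taken from diary dates and the published holiday and closure calendar of the child's region. Analyse the change in this rate in the linear mixed model already stated. An offset of log school days would not fit that model and would require a count model for this outcome. State in advance how a window with very few school days is handled.

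2. Add entry date (week −12) as one sine and one cosine term to the primary and secondary models, or at least as a prespecified sensitivity analysis. A further covariate for holiday days would largely duplicate these terms and is not needed.

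3. Report the distribution of entry months by arm, so that readers can see whether calendar balance was achieved.

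Cost: two degrees of freedom per model and one derived variable. No new patient data should be needed: diary entries are daily and region is the unit of randomisation, although the article does not say that region is held as an analysis variable, so this should be confirmed. Entry date precedes treatment and the school calendar is external to it, so neither adjustment removes a treatment effect.

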### Selection of sample

Children between 6 and 11 years of age with migraine with a statutory health insurance (approx. 90% of the population) and whose parents consent to participation are eligible for the study. Children are recruited by their pediatricians in practice. The pediatrician diagnoses migraine according to the International Classification of Headache Disorders 3rd edition (ICHD-3) [11], with the help of a standardized, electronic migraine checklist that was developed for the study.

Inclusion criteria are as follows:
Age 6 to 11 yearsDiagnosis of migraine (according to the International Classification of Diseases ICD-10, classification numbers G43.x), based on the International Classification of Headache Disorders (ICHD-3) [11] adapted to children (allowing shorter headache duration of 2 to 72 h, and bilateral instead of unilateral headache)History of migraine for at least 3 monthsAt least 3 headache days in the last 3 monthsMigraine prophylactic medication (beta-blocker, amitriptyline, topiramate) allowed if kept constant for the duration of the study

Exclusion criteria are:
Mental retardation (IQ < 70)Severe somatic or psychological, acute or chronic disease except headacheFamiliar hemiplegic migraine (genetically confirmed)Children will be excluded after the baseline phase if less than 3 headache days were present during the 3 months baseline phase

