### Sample size calculation

The primary outcome was defined as a difference in reduction of headache days between the baseline and the follow-up period of ≥2 headache days in 12 weeks. The significance level α was set at 0.05 and the power at 0.9. Power size calculation with these parameters shows that a sample of *n* = 279 in the intervention group A (pediatric practice) and *n* = 507 children in the intervention group B (interdisciplinary treatment in social pediatric centers) is needed. For the sample size calculation an intra-class correlation coefficient (ICC) of 0.1 was assumed.

The estimated number for recruitment is based on an analysis of the Barmer insurance database of 2017 [1]. Approximately *n* = 270,000 statuarily insured children at the age of 6 to 11 years are likely to obtain a diagnosis of a primary headache disorder. About 70% of these see a pediatrician for primary care. As approximately 20% of pediatricians in practice use the website “PädExpert”, which provides the electronic migraine checklist, inclusion and exclusion criteria and access to the study platform, we calculated that *n* = 28,350 children per year are available for screening of migraine at the pediatric practices. We estimate that of these, 17.5% in fact receive a migraine diagnosis, resulting in *n* = 4961 children.

Germany was divided in 77 regions according to the postal codes, in a way that every postal code region contained at least one social pediatric center. The postal code regions were then randomized at a 2:1 ratio to intervention B and to intervention A regions. We estimated that in 75% of the intervention B regions at least one social pediatric center would be willing to participate in the study. We assumed that up to 20% of children will be excluded after the baseline phase or drop out later in the study: 1) because of more than 33% of missing data in the electronic headache diary during the baseline phase or 2) because of less than three documented headache days during the 3 months baseline or 3) because of more than 66% of missing data in the electronic headache diary during the follow-up period or 4) because they are lost to follow-up.

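### The primary model omits baseline preventive treatment, which the app records in both groups and whose balance the recruitment design does not assure

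*Protocol article*

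**What the plan says.** Under Data analysis plan, the primary end point is analysed by a mixed linear regression "with the difference of headache days per 12 weeks from baseline to follow-up as dependent variable", with the intervention (yes/no) as predictor and random effects for the social pediatric centers. The adjustment is named: "Age, sex and headache frequency per 12 weeks at baseline are included as possible confounders". KINDL and PedMIDAS "at baseline are possible effect modifying elements and therefore integrated in the model as interaction effects". The same model serves the secondary outcomes.

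Under Selection of sample, preventive medication is "allowed if kept constant for the duration of the study". No such condition is set for non-drug measures. Under Measures, the app asks for "headache prophylactic measures taken in the last 3 months (within the categories: physiotherapy, trigger point therapy" and, further down the same list, medication. This is asked at the questionnaire time points: "Questionnaires are presented within the app at the start and end of the baseline" (weeks -12 and 0), and again at weeks 12 and 24.

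Under Sample size calculation, "The postal code regions were then randomized at a 2:1 ratio to intervention B and to intervention A regions". Selection of sample has children recruited by their own pediatricians. The article does not say whether those pediatricians know the allocation of their region.

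**The concern.** In a cluster trial, randomisation balances the regions. It does not by itself balance the children who are enrolled afterwards. If enrolment differs by group, baseline characteristics related to change in headache days can differ too. By listing possible confounders, the plan accepts that randomisation may not be enough.

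Preventive treatment is a natural candidate for that list. It may relate to how headache days develop, it is recorded in the same way in both groups, and part of it is outside the constancy condition, which covers medication and not physiotherapy or trigger point therapy. If its share differs between groups, the part not captured by the other covariates stays in the estimated effect. Because the model is reused, the secondary outcomes are exposed in the same way. Naming the covariate in advance also avoids a choice made after the baseline table is seen.

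**Working it through.** **1. The plan's own figures.** The stated sample size (279 in A, 507 in B) cannot be reproduced directly, because the article gives no SD and no cluster size. It can be solved backwards for scale:
- Standard error for 90% power at 2 days, two-sided 0.05: 2 / (1.960 + 1.282) = 0.617.
- Effective SD: 0.617 / √(1/279 + 1/507) = 0.617 / 0.0745 = 8.28 days, clustering included.
- With the stated ICC of 0.1 and assumed numbers of regions (26 in A, 37 to 51 in B), the individual SD is about 5.7 to 5.9 days, or 6.4 to 6.6 if the test is one-sided.

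None of these figures says anything about preventive treatment.

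**2. Assumed inputs, not in the article.** Share on preventive treatment p = 10 to 20%; difference in mean change between children with and without it d = 2 to 4 days; SD of change 7 days; difference in share between groups Δp = 10 points.

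**3. Shift of the estimate.** Shift = Δp × d.
- 0.10 × 2 = 0.2 day, 10% of the 2-day target.
- 0.10 × 4 = 0.4 day, 20% of the target.
- Wider range (Δp 2 to 20 points, d 1 to 4 days): 0.02 × 1 = 0.02 day to 0.20 × 4 = 0.8 day, or 1 to 40% of the target.

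The direction is unknown. Strictly, d should be the difference that remains after the covariates already in the model.

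**4. Effect on the test.** With standard error 0.617 and a normal approximation, the two-sided type I error is 0.062 at a shift of 0.2 day and 0.099 at 0.4 day. Enrolling more children shrinks the standard error but not the shift.

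**5. Precision.** R² = p(1 − p)d² / SD².
- p = 0.1, d = 2: 0.09 × 4 / 49 = 0.007; the standard error falls by 1 − √0.993 = 0.4%.
- p = 0.2, d = 4: 0.16 × 16 / 49 = 0.052; the standard error falls by 1 − √0.948 = 2.6%.

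This treats children as independent. With 279 / 26 = 10.7 children per region, the design effect is 1 + 9.7 × 0.1 = 1.97. A covariate that varies mainly within regions then removes about 0.052 / 1.97 = 2.6% of the variance, which is 1.3% of the standard error. With the smaller SD of 5.7, R² is 2.56 / 32.5 = 0.079, and 0.079 / 1.97 = 4.0% of the variance gives 2.0% of the standard error.

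**6. Does the change score already remove it?** Suppose children on preventive treatment have a stable mean level that differs by δ, and baseline and follow-up days have equal variance and within-group correlation ρ. The raw change does not differ between them. The planned model, however, also conditions on baseline days. At a given baseline count, the expected change differs by δ − ρδ = (1 − ρ)δ, which is zero only if ρ = 1. A stable level difference is therefore reduced, not necessarily removed. The article gives no ρ.

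**7. Which app entry.** Each entry looks back 3 months. The week -12 entry describes the time before enrolment. The week 0 entry describes the baseline phase, after enrolment in a region already allocated, and could itself be influenced by allocation.

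**The case against.** The strongest case is that nothing in the article is contradicted. A short list that includes the baseline value of the outcome is a sound choice, and almost any recorded baseline variable could be proposed in the same way. Further covariates may also appear in an analysis plan that is not shown. It stands that this is an improvement and not an error. But the article states a definite list, and preventive treatment differs from most other recorded variables in being treatment for the same condition.

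Baseline KINDL and PedMIDAS plausibly carry part of the severity that leads to preventive treatment. This stands: a reader might infer from the confounder sentence alone that three covariates are all the model has, and the next sentence shows otherwise. Neither scale measures treatment, so the overlap is partial.

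The constancy condition and the change score weaken the route through medication. This stands in part: they weaken it without closing it (step 6), and the condition does not reach non-drug measures.

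The magnitudes are assumed and probably on the high side. This stands. At 10% overall prevalence and a 279:507 split, a 10-point difference means 0.10 + 0.10 × 507/786 = 16% in A against 0.10 − 0.10 × 279/786 = 6% in B, or the reverse pattern: a large contrast. At 20% overall it would be 26% against 16%.

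Two stronger readings are tempting. A reader might infer that recruitment is open and that an imbalance exists; the article states neither, only the order of events and no concealment. A reader might also argue that earlier physiotherapy or trigger point therapy leaves less to gain from the group B programme, which has physiotherapeutic elements. That describes effect modification, which main-effect covariates do not address, so the case for the change does not rest on it.

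**Conclusion.** The point holds in a limited form. The stated primary model leaves out a relevant baseline variable that is already collected in both groups, in a design where enrolment after allocation does not assure its balance. Whether any bias will arise cannot be known from the article. On the assumed values the shift is 0.2 to 0.4 day against a 2-day target, less if the other covariates absorb part of it, and the gain in precision is at most about 2 to 3%. The matter is minor and does not put the primary comparison in doubt.

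**What to change.** Add two main-effect covariates to the primary model, and so to the secondary models that reuse it, both taken from the week -12 app entry:
- preventive medication in the preceding 3 months (yes/no);
- physiotherapy or trigger point therapy in the preceding 3 months (yes/no).

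Do not use the week 0 entry, for the reason in step 7. State how an unanswered item is handled, so that no child leaves the primary analysis because of it.

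The cost is two degrees of freedom and a line in the analysis plan; no new data are needed. If the sponsor prefers to keep the primary model as it is, the same two covariates can be prespecified as a sensitivity analysis.
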